### Sample size

Based on data from an unpublished cohort study performed at Hvidovre Hospital, 25 consecutively included older medical patients had a mean change in the de Morton Mobility Index (DEMMI) [62] score of 1.8 and a standard deviation of 12.8 from admission to 1 month after discharge. A change of 10 points in the DEMMI score is considered a minimal clinically important difference in acute older medical patients [62]. To be able to detect a 10-point difference in the between-group change in the DEMMI score at the 4-week assessment (primary end point), we will need a sample size of 27 patients per study arm to obtain a type I error rate of 5 % and a power of 80 % for a two-sample *t* test of a normal mean difference with a two-sided significance level. We will continue to recruit patients until 54 patients have been assessed for the primary end point (4 weeks). In case of a skewed distribution of patients in the two groups (intervention and control), we will recruit until both groups contain 25 patients. We expect a maximum of 80 patients to be included in the study.

### Study principles

The protocol follows the SPIRIT 2013 (Standard Protocol Items: Recommendations for Interventional Trials) checklist [63] and the description of the intervention follows the Template for Intervention Description and Replication (TIDieR) checklist [64]. The reporting of the study once completed will follow the CONSORT (Consolidated Standards of Reporting Trials) Statement, using the extension for non-pharmacological trials [65].

### Study groups

#### Control group

Patients in the control group will receive routine care during hospitalization and after discharge. No efforts will be made to change this care during the study period. Routine care will be used as a comparator to reflect the current care for these patients.

According to the Danish Healthcare Quality Program (DDKM) [66], the functional level and nutritional status of hospitalized patients must be described within 24–48 h after admission [67] and treatment planned accordingly. No standard involves in-hospital training [67], but patients needing recovery (e.g. rehabilitation) should be identified [68], and rehabilitation (including exercise) should be planned to target the patient’s impairment and limitations. Often rehabilitation starts during hospitalization, and if it continues after discharge a rehabilitation plan must be prepared by the hospital. At Hvidovre Hospital around 5 % of older medical patients are discharged with a rehabilitation plan (personal communication with geriatric team in the ED, 30 October 2015) involving exercise therapy supervised by physiotherapists.

### Intervention group

Patients in the intervention group will receive 1:1 supervised progressive strength training daily on weekdays during hospitalization and three times per week for 4 weeks (12 training sessions, 1:1 supervised) after discharge. To account for possible cancellations, i.e. due to illness or other obstacles for training completion, distributing the 12 in-home training sessions over a maximum of 5 weeks will be allowed. The training will take place in the patient’s bedroom during hospitalization and in the patient’s own home after discharge.

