Therefore, the aim of this study is to determine in a randomized, investigator-blinded controlled trial whether a simple, low-technology, supervised strength training program for the lower extremities, combined with post-training protein supplementation initiated during hospitalization and continued at home for 4 weeks after discharge, is superior to usual care on change in mobility 4 weeks after discharge in older medical patients.

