Health condition(s) or problem(s) studied	Progressive strength training in older medical patients
Intervention(s)	Intervention: strength training daily during hospitalization and 3 times per week for 4 weeks after discharge
	Control: usual care
Key inclusion and exclusion criteria	Inclusion criteria: age ≥65 years; acutely admitted from own home to the Emergency Department at Hvidovre Hospital, Denmark
	Exclusion criteria: terminal illness; in treatment for a diagnosed cancer; diagnosis of chronic obstructive pulmonary disease (COPD) and participation in a COPD rehabilitation program; living outside the municipalities of Copenhagen and Broendby; inability to speak or understand Danish; inability to cooperate in tests/exercises; an expected hospitalization >24 h; assigned to physical rehabilitation in the community; a Cumulated Ambulation Score (CAS) of 0 in the sit-to-stand item
Study type	Interventional
	Allocation: randomized
	Blinding: investigator blind
Date of first enrollment	September 2013
Target sample size	80
Recruitment status	Recruiting
Primary outcome(s)	The de Morton Mobility Index
	Timeframe: change from baseline to 4 weeks after discharge (end of intervention)
Key secondary outcomes	24-h mobility measured by *activ*PAL3^TM^; isometric knee extension strength in the dominant leg; the 30-sec sit-to-stand test; habitual gait speed; hand-grip strength in dominant hand; the Barthel Index 20

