### Study setting

The study will be conducted at Copenhagen University Hospital, Hvidovre, Denmark and in the participants’ own homes in the municipalities of Copenhagen, and Broendby. Hvidovre Hospital has a 552-bed capacity. Recruitment will take place in the 20-bed Emergency Department (ED) through which the majority of older medical patients (65 years or older) are admitted. There are approximately 4000 admissions of older medical patients to the ED every year, and around 50 % are discharged within the first 24 h. In Denmark, the healthcare system is public and provides feeless, tax-paid primary medical care, hospital treatment, and homecare services uniformly for all citizens.

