### Study sample and recruitment procedure

Older medical patients (65 years or older) acutely admitted from their own homes to the medical services of the hospital will be included by random sampling within 24 h of admission. Each day (Monday to Friday) the primary investigator or one of three assistant investigators will receive a computer-generated list of all newly admitted older medical patients (65 years or older). The investigator will check the medical records of all the listed patients to determine their eligibility according to the inclusion and exclusion criteria as listed below:

**Inclusion criteria**Age 65 years or olderAdmitted from own home to medical services of the hospital

**Exclusion criteria**Terminal illnessIn treatment for diagnosed cancerDiagnosis of chronic obstructive pulmonary disease (COPD) and participation in a COPD rehabilitation programLiving outside the municipalities of Copenhagen and BroendbyInability to speak or understand DanishInability to cooperate in tests/exercisesTransferred to the intensive care unit or isolation-room stayAn expected hospitalization of at least 24 hAssigned to physical rehabilitation in the municipalityA Cumulated Ambulation Score (CAS) of 0 in the sit-to-stand item

Eligible patients will be visited on the ward by one of four investigators where they will be given a written description of the study to read and will be informed about the study verbally. The investigators will ensure that all questions are answered before the patient is asked to participate in the study. The Ethics Committee of the Capital Region has granted an exemption for the 24-h consent time, which is normal practice when including patients for medical research in Denmark. The exemption was granted to be able to follow the patients through their entire hospitalization and to assess their functional level before an effect of medical treatment is seen. Patients who agree to participate will be asked to sign an informed consent form to be included in the study. The patient will keep the original document and two copies will be archived.

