### Secondary outcome measures

Secondary outcomes will be the following six: (1) 24-h mobility measured by an *activ*PAL3™ activity monitor (PAL Technologies Ltd., Glasgow, UK). The patient will be asked to wear an *activ*PAL3™ on the thigh during hospitalization, the first week after discharge, the first week after the 4-week assessment and the first week after the 6-month assessment. The patient will wear the *activ*PAL3™ halfway between the spina iliaca anterior superior and the patella on the front side of the right thigh. The monitor will be covered in Tegaderm™ transparent waterproof film (3 M, Maplewood, MN, USA), attached to the patient by a PAL*stickie*™ (dual-layer hydrogel adhesive pad) and covered by Leukomed® T transparent film (BNS medical, Hamburg, Germany) to enable the patient to wear the *activ*PAL3™ while showering. The patient will be asked to wear the monitor for 24 h per day. The *activ*PAL3™ can record continuously for 7 days, whereafter the monitor will be replaced should the hospitalization be of a longer duration. The *activ*Pal3™ accelerometer measures time spent sitting/lying, standing and walking, the number of steps taken, cadence and the number of sit-to-stand and stand-to-sit transitions. The *activ*Pal3™ is a valid and reliable measure of posture and transitions in healthy young and mobility limited older adults [75–77] and of walking at speeds between 0.67 m/s and 1.56 m/s in young and older adults [78–80]. Unpublished data from Hvidovre Hospital regarding 317 older medical patients has shown that 46 % of them walked at speeds below 0.67 m/s, why time spent walking could potentially be categorized as standing for 46 % of older medical patients. For this reason, if 15 % of the total sample walk at speeds below 0.67 m/s the *activ*Pal3™ data will be dichotomized into sedentary (sitting/lying) and upright time (walking/standing); (2) isometric knee extension strength (IKE) in the dominant leg using a handheld dynamometer (Power Track II Commander; JTech Medical, Midvale, UT, USA). The patient will be seated in a standard chair with a seat height of approximately 45 cm, with the arms crossed over their chest and 90° knee flexion [81, 82]. A strap will be attached to the chair and the patient’s ankle, just proximal to the malleoli. A transducer will be placed under the strap and a thin foam pad will be placed between the transducer and the leg. The distance between the lateral femoral epicondyle and the center of the transducer will be measured (the moment arm). The patient will be asked to extend the leg as forcefully as possible for 5 s three times with a 1-min pause in between. Up to two additional contractions will be performed if the last contraction elicits the highest value to ensure that maximal force is measured. Isometric knee extension strength will be expressed as maximal force (Nm) per kg body weight (kg); (3) the 30-sec sit-to-stand test (STS) using a standard armchair with a seat height of 45 cm [83]. The patient will be asked to sit with the arms crossed over the chest and to stand up once without using the arms. If this is performed safely, the patient will be asked to stand up fully and sit down as many times as possible in 30 s with the arms across the chest. The number of full stands will be counted. If the patient is not able to rise once from the chair without using the arms, a modified STS will be used, allowing the patient to use the armrests for support; (4) habitual gait speed (HG) on a 4-m course [84, 85]. The patient will be asked to walk 4 m at usual pace starting from a standing position. A walking aid will be allowed if needed. The faster of two walks will be used as the outcome; (5) hand-grip strength (HGS) in the dominant hand using a handheld dynamometer (Digi-II; Saehan). The patient will be placed in a sitting position in an armchair, with the lower arm placed on the armrest, an elbow flexion of 90° and the wrist in a neutral position. The patient will be asked to place the contralateral hand on the leg with the palm facing upwards. The dynamometer handle will be set at position 2 [86] and the investigator will reset the dynamometer before handing it to the patient and will ask the patient to squeeze the handle as forcefully as possible for 5 s. The patient will be asked to perform the test three times with a 1-min pause in between. If the third test shows the highest value additional tests will be performed until performance of a lower value to ensure that the highest value possible is obtained. Hand-grip strength will be expressed in kg; (6) the Barthel Index 20 (BI) is used as a measure of Activities of Daily Living (ADL) [87]. The BI assesses the help needed in regard to grooming, toilet use, feeding, transfer, mobility, dressing, stair climbing and bathing, and in addition the presence or absence of urinary and fecal incontinence. A score of between 0 and 20 can be obtained with higher scores indicating less disability.

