### Data collection

The primary investigator and a team of three assistant investigators will perform all baseline and follow-up assessments. All four investigators are trained physiotherapists with 1 to 15 years of experience.

The admission assessments will be performed on the acute medical admissions ward or on an internal medicine ward at Copenhagen University Hospital, Hvidovre, Denmark, within the first 48 h after admission. All follow-up assessments will be performed in the patient’s own home, and the same investigator will assess the same patient at all assessments whenever logistically possible, to promote patient retention.

During each training session the supervising physiotherapist will complete an exercise diary consisting of information about the level of exercise attained according to the progression models, the extra load added (kg), and the number of sets and repetitions performed at each level. Self-reported pain will be registered immediately before and after each training session by the use of the VRS. Moreover, the physiotherapist will register reasons for non-participation as well as the amount of protein consumed after each training session. The patient time line including data collection is presented in Table 3.

**Table 3 Tab3:** Patient timeline

	Study period						
Time point	Admission	Baseline	Hospital intervention	Discharge assessment	Home intervention	4-week assessment	6-month assessment
		≤48 h after admission	Daily during hospitalization	In patient’s home	3 times per week for 4 weeks in patient’s home	In patient’s home	In patient’s home
Enrollment							
Eligibility screen	X						
Informed consent	X						
Study groups							
Strength training		X	X	X	X	X	X
Control		X		X		X	X
Assessments							
Baseline assessment^a^		X					
Primary outcomes		X		X		X	X
Secondary outcomes		X		X		X	X
Descriptive variables and possible confounders and modifiers		X		X		X	X

^a^See Table 2 for a detailed description of assessed variables

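### The expected-stay criterion is stated backwards: both eligibility lists exclude patients expected to stay 24 h or longer, which contradicts a programme that starts in hospital

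*Protocol article*

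**What the plan says.** Two places in the protocol article state the criterion, both as an exclusion:

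- *Study sample and recruitment procedure*: the exclusion list contains an expected hospital stay of 24 h or more.
- Table 1 (*Study design*): the exclusions include "an expected hospitalization >24 h".

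Other sections describe what happens to patients in hospital:

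- *Background and rationale* (aim): strength training "combined with post-training protein supplementation initiated during hospitalization and continued at home for 4 weeks after discharge".
- *Intervention group*: "Patients in the intervention group will receive 1:1 supervised progressive strength training daily on weekdays during hospitalization".
- *Study sample and recruitment procedure*: patients "will be included by random sampling within 24 h of admission".
- *Data collection*: baseline is assessed on a ward "within the first 48 h after admission". Randomization follows baseline.
- *Secondary outcome measures*: the activity monitor is worn in hospital and records for 7 days, "whereafter the monitor will be replaced should the hospitalization be of a longer duration".
- *Secondary and supplementary analyses*: an effect during hospitalization is estimated, with a sub-analysis adjusted for length of stay.

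*Changes to initial plan* records an added municipality, the dropping of the community-rehabilitation exclusion and a new screening procedure. It says nothing about expected stay, so the criterion is current text.

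**The concern.** Eligibility defines the population to which the result applies. Here it is a working rule, applied by four investigators and, from January 2015, by a screening physician. Read as written, it admits only patients who are expected to be gone within a day. The trial's distinguishing feature is training that starts in hospital and continues at home, and such patients have almost no time for the first part.

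There are two possibilities, and each does harm:

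- **Screeners followed the text.** The sample then consists mainly of patients with little in-hospital training, and the comparison is close to one of home training against usual care.
- **Screeners followed the evident intention.** The sample is then sound, but the published criteria describe the wrong patients. Anyone repeating the trial or judging whether it applies to their own wards would be misled.

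**Working it through.** **1. Is it a slip of text extraction?** Unlikely. One list gives the criterion in words and the other with a symbol. Both stand in intact exclusion lists and point the same way. They differ only at the boundary: the Methods list excludes a stay of exactly 24 h, and Table 1 does not.

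**2. Criterion against design.** For a patient expected to leave within 24 h:

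| Element of the plan | What it needs | Under the criterion as written |
|---|---|---|
| Inclusion within 24 h of admission | Some stay left after consent | Most or all of the expected stay may be used up |
| Ward baseline up to 48 h, then randomization | Presence on the ward up to 48 h | The second half of the window is open only to patients who outstay their expected time |
| Training on each weekday of the stay | Several weekdays | At most about one session |
| Monitor replaced after 7 days | Some stays beyond a week | Only by large departures from the expected stay |
| Length-of-stay adjustment | Real variation in stay | Little variation expected |

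Nothing else in the article supports the criterion in its stated direction.

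**3. Share of training given in hospital.** *Intervention group* plans 12 home sessions. With at most about one hospital session, the in-hospital share is 1 / (1 + 12) = 1/13 = 7.7 %. With none, it is 0 %. This assumes that the actual stay is also under 24 h.

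**4. Scale at the hospital, as context only.** *Study setting* states: "There are approximately 4000 admissions of older medical patients to the ED every year", and "around 50 % are discharged within the first 24 h". So 4000 × 0.50 = about 2000 a year leave within 24 h, and 4000 − 2000 = about 2000 stay longer. These are all older medical admissions, before any other exclusion, and the split applies to the criterion only if expected stay tracks actual stay. With at most 80 patients to be included, these are not numbers of trial patients gained or lost.

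**5. Sample size.** The plan's 27 per arm reproduces from a difference of 10 and an SD of 12.8. The normal approximation is n = 2 × (1.960 + 0.842)² × 12.8² / 10² = 25.7, so 26. The exact two-sample t test needs 26.7, so 27, with power 0.804. This calculation does not use the stay criterion.

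**The case against.** The strongest reply is that this is a wording slip that nobody would have followed. The whole article describes in-hospital training, two physiotherapists are assigned to it, and recruitment had been running since 2013. Staff who screened for such a programme would hardly have turned away the patients who stay. That is plausible, and it makes a reporting error the likelier harm. It does not remove the need for a correction, because the lists are what a reader or a new screener would use.

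A second reply is that expected stay is not actual stay. This stands. A patient expected to leave within a day may remain for several, so some in-hospital sessions, later baselines and even monitor replacements could occur under the literal rule.

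A reader might go further and infer that the trial was run on short-stay patients, or that the in-hospital effect and in-hospital monitor data could not exist. The article supports neither:

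- It does not report which rule was applied.
- The first contrast in the primary model is discharge minus baseline, and the discharge test is done at home. It can be computed for any patient with both assessments.
- Monitor records from hospital would be short, not absent.

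The weaker statement holds: under the literal rule that contrast would reflect little in-hospital training.

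**Conclusion.** The point holds as an internal contradiction in an eligibility criterion. It appears in two places and no listed change corrects it. The error lies in the two exclusion lists, not in the training schedule. The most likely explanation is an inverted wording.

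The size depends on what screeners did. If they followed the text, the in-hospital component is largely defeated, with roughly 0 to 8 % of planned sessions in hospital for patients whose actual stay matches the expectation. If they did the opposite, the conduct of the trial is unharmed and the fault is a misstated study population. The documents cannot decide between these. The correction is needed either way, because the error concerns who may enter the trial. The primary analysis and the sample-size calculation need no change on this account.

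**What to change.** - Correct the direction in the Methods exclusion list and in Table 1, so that patients expected to be discharged within 24 h are excluded. Alternatively, move an expected stay of at least 24 h to the inclusion criteria.
- Use the same boundary in both places.
- Check the registry entry. Table 1 is headed as registration data, but the registry record itself is not at hand, so whether it carries the same wording is unknown. Correct it if it does.
- Check the screening log to establish which rule was applied, and report in the flow diagram any patients excluded under the reversed wording.

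The cost is one line in each of two places, possibly one in the registry, and a review of existing logs. No extra patients, visits or analyses are needed.

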#### Training intervention

All training sessions will be supervised by a skilled physiotherapist. Two physiotherapists with 3 years of experience will supervise the in-hospital training sessions and five physiotherapists with 4–15 years of experience will supervise the at-home sessions. Physiotherapists working on the medical wards of the hospital and physiotherapists involved in geriatric rehabilitation in the involved municipalities were offered participation in the study. All involved physiotherapists volunteered to participate and were granted the time needed to supervise the exercise sessions during working hours. In every training session, the patient will be asked to perform a warm-up program consisting of seated exercises for the lower extremities (hip flexions, knee extensions, heel raises, hip abductions/adductions). The patient will be asked to perform each exercise for 20 repetitions. The warm-up program has a duration of 5 min.

After warm-up, the patient will be asked to perform a progressive strength training program for the lower extremities, based on a minimum treatment approach, consisting of a sit-to-stand exercise (Fig. 2) and a heel raise exercise (Fig. 3) as outlined in detail below. For both exercises the progression will follow pre-defined models based on the STAND model (Fig. 2), which we have tested and found feasible in older medical patients [61]. In each exercise, the progression model allows for performing the exercise from a seated position (level 1) to performing the exercise unilaterally with extra load added (level 7/level 8). The patient will be asked to perform three sets of 12 repetitions maximum (RM) of each exercise. This will correspond to 60–70 % of 1 RM [30, 69, 70]. The aim will be to reach contraction failure (muscular fatigue) at a relative load zone of 8–12 RM in each set [30]. A 2-min pause will be allowed between sets [30]. The correct level of each exercise will be chosen according to the progression models by the supervising physiotherapist. The patient will be asked to work at moderate velocity taking 2 s for the concentric (raising) phase and 2 s for the eccentric (lowering) phase of the exercise. An isometric pause of 1 s will be allowed after both the concentric and the eccentric phase [30]. If a patient can perform six non-compensatory repetitions and needs a little support performing the last repetitions (e.g. minimal use of armrests/minimal balance support), and if a proper technique is maintained, training at the given level will be accepted to enable the patients to reach fatigue in every set. Moreover, increased speed will be allowed in the last two repetitions of each set to optimize leg power, which has been shown to be associated with physical performance in mobility-limited older adults [54, 71]. Each set of each exercise is considered unique and determines whether the patient will stay on the same level or either progress or regress. The total duration of each exercise session will be approximately 10–15 min.

